## Discussion

The implications of the study are to provide estimations on the efficacy of the POSITIVE system in reducing frailty symptoms among older adults, prevent disability and dependency, as well as to affect several other health-related domains. Further, the study will contribute knowledge about the feasibility of the current study design in Sweden, perceived value of the POSITIVE system, its utility and the acceptability of the POSITIVE system among the different stakeholders. Thus, the study will give relevant data to inform powered studies of efficacy and effectiveness.

Our primary objective relates to improving frailty in at least one criterion. The multicomponent intervention addresses frailty as a clinical entity, measured with the Linda Fried’s criteria and with FTS-5. The multicomponent intervention we administer is known to be effective, but we are also exploring whether the support of our technology boots its effect. The two frailty scales have common items, such as grip strength, gait speed and level of physical activity, and we do not expect to see great differences between the scales. In the case we find any differences during the data analysis, we will discuss the possible effects of the intervention on the items that are not repeated, including weight loss and exhaustion in the case of the Fried’s scale, and balance and body mass index in the case of the FTS-5. Further, we will discuss the suitability of the different assessment tools to be used in future powered studies.

Limitations in this study include the challenges in blinding the assessor, since the study is not blinded for the participants, and they may reveal their allocated group to the assessor. However, the participants will be reminded in all contacts with the assessor not to reveal whether they are using the POSITIVE system or not. Another limitation is that the selection process of the participants will not be randomised, but the potential participants will be invited to contact the research group voluntarily if they are interested in the study. This fact may lead to selection bias considering that the study participants may not provide a heterogenous and representative sample of the older adult population in Sweden.

Lastly, even though the aim in this study is to have a cohort comparable to that of Spain and Poland which are part of the main POSITIVE project, the differences in the organisation of the health care system causes certain differences in the study processes and in the clinical praxis, and these should be considered when doing cross-cohort analysis in the main project.

Possible practical issues during the study may involve technical aspects, since many older adults may not be familiar with how to handle the technical equipment. However, a researcher from KTH will provide participants with support during the whole study, if needed. Another issue which may affect the study processes and participant recruitment is the current pandemic situation in the world, which in turn may negatively affect the recruitment of participants.

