**Methods:**

The primary objectives are to estimate the potential efficacy of the POSITIVE system on improving frailty in at least one point in Fried’s criteria and five points in Frailty Trait Scale. The secondary objectives are to (A) assess the recruitment, retention, drop-out rates, compliance with the intervention and the intervention mechanisms of impact; (B) evaluate the usability and acceptance of the POSITIVE system, and to get estimations on; (C) the potential efficacy of the intervention on improving the participants’ physical performance, cognitive functions, mood, independency level in activities in daily living, the impact on quality of life and number of falls during the follow-up period; (D) the impact on the caregiver quality of life and caregiver burden; and (E) on the consumption of health care resources, participants’ perception of health and level of care received, and healthcare professionals’ workload and satisfaction.

A randomised controlled, assessor-blinded pilot study design recruiting from a primary care centre in Stockholm Region will be conducted. Fifty older adults identified as pre-frail or frail will be randomised into a control or an intervention group. Both groups will receive a medical review, nutritional recommendations and Vivifrail physical exercise program. The intervention group will receive the POSITIVE-system including a tablet, the POSITIVE application and portable measurement devices. The participants receiving the POSITIVE program will be monitored remotely by a primary care nurse during a 6-month follow-up. Data will be collected at baseline, 3 and 6 months into the intervention though the platform, standardised assessments and surveys. A process evaluation as per Medical Research Council guidance will be conducted after the 6-month follow-up period.

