### Trial design

This is a randomised-controlled, single-blinded and prospective pilot study. The study processes are presented Fig. 1. Within the protocol, a process evaluation is scheduled and will be conducted in line with Medical Research Council (MRC) guidance for process evaluations. The components in the evaluation will follow the guidelines regarding the context, implementation level activities and mechanism of impact, such as participant’s responses to and interactions with the interventions [26].

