**Fig. 3 Fig3:**
[figure not shown]
The POSITIVE system and its different components and users

Results from physical tests will be automatically registered in the platform once the sensors send the data to the tablet via Bluetooth. These sensors include a gait speed placed on the floor (does not measure steps), a device to measure power in the lower limbs by monitoring the chair stand test, which will be placed on the thigh, and a smart weight scale to track involuntary weight loss (See Fig. 4).

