### Data collection

A technical researcher from KTH will collect data received from the POSITIVE platform. The server for the POSITIVE platform will be provided by Amazon Web Services. This service meets General Data Protection Regulation (GDPR) requirements [35] in terms of security and encryption of personal data, ability to restore the availability and access to personal data in a timely manner in the event of a physical or technical incidence. It also meets requirements for regularly testing, assessing and evaluating the effectiveness of technical and organizational measures for ensuring the security of processing. Further, the technology and methodology in the pilot meets security requirements, since pseudonymized data will be used. The pilot complies with the International Organization for Standardization (ISO) 27001 standards on information management security, and Hypertext Transfer Protocol Secure (HTTPS) is used for all connections.

The data collection in the periodic follow-ups will be conducted by a blinded research assistant. The data collection flow is shown in Fig. 1. The research assistant will write field notes after each contact with the participant to describe and understand the context.

The quantitative and qualitative data from the older adults and caregivers will be collected partly during home visits and partly through phone calls. Data from the informal caregivers will be collected through posted surveys if the caregivers do not live in the same household. Demographics from the participants and their caregivers, which will be collected consists of background data (age, comorbidities, type of housing, relationship to the older adult, employment, etc.). The participants’ health care resource consumption and their overall level or physical activity will be assessed at baseline, 3 and 6 months into the intervention (See Fig. 2).

Data collected from health care professionals will be collected through surveys and qualitative interviews at 2 weeks, 3 and 6 months into the intervention. The surveys consist of background data (age, education, number of working years, etc.) and structured questionnaires. The interviews will be conducted by a researcher focusing on the use of technology and the implementation processes.

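### The assessor-blinding safeguard covers what participants say but not what the assessor sees in homes holding the study equipment

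*Protocol article*

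**What the plan says.** The Trial design section states: "This is a randomised-controlled, single-blinded and prospective pilot study". The abstract specifies that it is the assessor who is blinded. Data collection adds: "The data collection in the periodic follow-ups will be conducted by a blinded research assistant". The same section says that data from the older adults and caregivers "will be collected partly during home visits and partly through phone calls". No clinic or other place for in-person assessment is named.

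The equipment differs by arm. From the abstract: "The intervention group will receive the POSITIVE-system including a tablet, the POSITIVE application and portable measurement devices". The section on the home monitoring system describes the devices. It begins "These sensors include a gait speed placed on the floor" and goes on to a thigh-worn device for the chair stand test and a smart weight scale. Intervention participants are monitored with this system for 6 months. Control participants instead record their exercise in daily logbooks (Secondary feasibility outcomes).

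The Discussion lists assessor blinding as a limitation. The reason given is that participants know their group and may disclose it, and the stated countermeasure is that "participants will be reminded in all contacts with the assessor not to reveal whether they are using the POSITIVE system or not".

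**The concern.** The countermeasure answers one threat, disclosure by speech. The setting creates a second, sight: the person who must stay blind enters homes whose contents differ by arm. If equipment is usually visible in intervention homes, its absence also hints at control, so the route is not confined to one arm.

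Both arms receive the medical review, nutritional advice and Vivifrail programme, so the comparison isolates the added technology. Any such effect may be modest, and a modest assessor bias could be mistaken for it. The Fried objective is an improvement of a single point, the FTS-5 objective is five points, and testing is one-tailed at 0.05. Bias in favour of the system would therefore raise the false-positive rate directly. The estimates are also meant to inform later powered studies, which would inherit the bias.

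**Working it through.** The article gives no unblinding rate and no power calculation, so there is no stated figure to reproduce. The main check is textual.

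1. **Who and where.** The blinded assistant does the periodic follow-ups. Participants' data come from home visits and phone calls (Data collection).
2. **Does the primary outcome need a visit?** The Discussion says Fried's criteria and FTS-5 share grip strength, gait speed and physical activity level. The first two need an in-person test, and the home is the only in-person setting named. Figs. 1 and 2 are not shown, so this is a strong inference rather than a quoted statement.
3. **What is in the home?** Intervention: tablet, floor sensor, thigh device, smart scale. Control: none of these, but a logbook.
4. **What does the safeguard cover?** It covers whether the participant reveals use of the system. Following it to the letter does not require anything to be put out of sight.
5. **Does separation of roles close the gap?** A technical researcher installs the system and collects usability data by phone, and allocation is done by someone outside screening. These steps limit other routes to unblinding. None of them stops the assessor seeing the devices during a visit.

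**Illustration of frequency.** Let *p* be the assumed chance that equipment is noticed at one visit. Assume that the 3- and 6-month follow-ups are both home visits and are independent. The share of intervention homes unmasked at least once is 1 − (1 − *p*)². The 25 per group is from Sample size and power considerations.

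| *p* (assumed) | Share unmasked by 6 months | Homes of 25 |
|---|---|---|
| 0.10 | 1 − 0.90² = 0.19 | 4.7 |
| 0.25 | 1 − 0.75² = 0.44 | 10.9 |
| 0.50 | 1 − 0.50² = 0.75 | 18.8 |
| 0.75 | 1 − 0.25² = 0.94 | 23.4 |
| 0.90 | 1 − 0.10² = 0.99 | 24.8 |

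**Illustration of consequence.** Suppose assessor bias moves the FTS-5 group difference by *b* points in favour of the system when there is no true effect. For a simple comparison of two means with 25 per arm, the one-sided error is Φ(*b* / (SD × √(2/25)) − 1.645), where √(2/25) = 0.283. With *b* = 1 and SD = 6, this is Φ(1/1.697 − 1.645) = Φ(−1.056) = 0.146.

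| *b* (assumed) | SD 6 | SD 8 | SD 10 |
|---|---|---|---|
| 0 | 0.050 | 0.050 | 0.050 |
| 1 | 0.146 | 0.115 | 0.098 |
| 2 | 0.320 | 0.223 | 0.174 |

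Here *b* is the net group shift. A shift of 2 points in each unmasked participant at *p* = 0.25 would give about 2 × 0.44 = 0.88 points. None of the *p*, *b* or SD values comes from the article.

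**The case against.** The authors already declare assessor blinding a limitation, the study is a small pilot without a power calculation, and a journal article leaves visit instructions to the full protocol. The last point would settle the matter if the article were silent. It is not: it names the threat, its cause and the remedy, and that remedy falls short when followed as written.

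Several stronger readings are tempting, but the text does not support them.

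- **That blinding will often fail.** No rate is given. The devices are described as portable and could be put away between uses. The 19% to 99% range shows that the answer depends wholly on the assumed *p*.
- **That the reminder is the only protection of any kind.** Installation, usability interviews and allocation are kept away from the assessor or from screening, which removes some of the main occasions for talking about the system.
- **That the field notes invite discussion of system use.** The text is "The research assistant will write field notes after each contact with the participant to describe and understand the context". It does not say that the notes cover the system, and such notes might even capture an unblinding event.
- **That the assessor handles the control logbooks.** The article does not say who collects them.
- **That the bias can be sized against the precision of a responder difference.** Both the responder rates and the shift would have to be assumed.

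Exhaustion, a Fried item, is self-reported. Its main exposure is the unblinded participant, and hiding equipment does nothing for that.

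**Conclusion.** The concern holds in a limited form. As written, the stated safeguard leaves the visual route open, and the primary outcome is exposed to it through the tests that must be done in person. The plan supports the statement that blinding is at risk, not that it will fail. The frequency and the resulting bias are unknown, and the figures above show only that a shift of 1 or 2 FTS-5 points would matter at this sample size under the assumed SDs. The conclusion rests on one inference, that grip strength and gait speed are tested at the home visits. It is an inexpensive improvement worth making, not a flaw that invalidates the design.

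**What to change.** 1. When each home visit is booked, have someone other than the assessor (the technical researcher or the nurse) ask intervention participants to put the tablet and sensors out of sight, and control participants to do the same with their exercise logbooks.
2. At 3 and 6 months, have the assessor record whether unblinding occurred, the guessed arm and the reason.
3. Report the unblinding rate by arm as a feasibility result, which suits a pilot meant to inform the design of powered studies. Do not analyse frailty by correct or incorrect guess: that would split about 25 people per arm on a post-randomisation variable that the outcome itself can influence.
4. Name the visual route in the limitations.

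The cost is one extra line in the booking call, one form item and a small burden on participants. The last follow-up was scheduled for October 2021. If the visits are complete, item 4 still applies to this study's report, and items 1 to 3 belong in the design of the powered study.

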## Data Availability

The datasets used and/or analysed during the current study, as well as questionnaires and interview guides are available from the corresponding author on reasonable request.

## Abbreviations

ADL: Activities in daily life
CG: Control group
FTS: Frailty Trait Scale
GP: General practitioner
GDPR: General Data Protection Regulation
GDS-S: Geriatric Depression Scale—Swedish version
HCRS: Health care resources consumption
ICT: Information and Communication Technology
IG: Intervention group
ISO: International Organization for Standardization
KI: Karolinska Institute
KTH: The Royal School of Technology
LAR: Legally acceptable representative
MNA-S: Mini Nutritional Assessment Short Version
MoCA: Montreal Cognitive Assessment
MRC: Medical Research Council
NASA-TLX: National Aeronautics and Space Administration Task Load Index
PCC: Primary Care Centre
POSITIVE: Maintaining and Improving the Intrinsic Capacity Involving Primary Care and Caregivers
QS: Questionnaires
QSOM: Questionnaire on the Organisational Model
SPIRIT: Standard Protocol Items: Recommendations for Interventional Trials
SPPB: Short Physical Performance Battery
SUS: System Usability Scale
UEQS: User Experience Questionnaire
WHO: World Health Organization
WHODAS: World Health Organization Disability Assessment Schedule
